#### Secondary outcomes

Self-reliance is measured with the WHODAS II [68]. This questionnaire is based on an international classification system and is used when assessing the level of functioning of a person with an emphasis on activities and participation level. The WHODAS II measures the following domains: understanding and communicating, mobility, self-care, interaction with people, household and activities, and participation in society. The questionnaire focuses on the last 30 days and consists of twelve items. Higher scores indicate a lower self-reliance. Test-retest studies of the 36-item scale in countries across the world found it to be highly reliable [68].

Health Related Quality of Life is measured with the SF-12v2 questionnaire which measures eight health domains to assess mental and physical health and consists of twelve questions [69]. Mental health-related scales include vitality, social functioning, role emotional, and mental health. Physical health-related domains include general health, physical functioning, role physical, and body pain. A high score corresponds to a better health condition. The instrument has been validated across a number of chronic diseases and conditions [69, 70].

Experienced feelings of loneliness are measured with de Jong Gierveld Loneliness Scale [71]. The questionnaire is a reliable and valid measurement instrument for overall, emotional, and social loneliness and consists of six items using a 10-point scale, ranging from 1 (not lonely) to 10 (extremely lonely).

#### Other relevant measures

Demographic and chronic disease related characteristics including age, gender, marital status, body mass index (BMI), educational level, income, degree of limitation regarding chronic illness(es) are assessed. BMI is defined as body mass divided by the square of body height. Educational level is categorized into low (i.e. primary, basic vocational, or lower general school), moderate (i.e. medium vocational school, higher general secondary education, and preparatory academic education), or high (i.e. higher vocational school or university level) according to the Dutch educational system. The degree of impairment is measured with a self-report questionnaire [38]. The participant states for 14 common chronic illnesses (i.e. cardiovascular, osteoarthritis) and physical conditions (i.e. hearing or visually impaired) to what degree he/she is limited in his/her PA behavior by one of the mentioned diseases or by another not mentioned disease. For each chronic illness, the participant scores the degree of impairment on a 5-point scale ranging from 0 = not applicable, 1 = not at all/hardly, 2 = a little, 3 = very, to 4 = extremely.

#### Sample size and statistical power

Sample size calculations are based on the primary outcome measures of CF. Based on literature on the effects of PA on CF (i.e. Memory, Set shifting, Inhibition of pre-potent responses and Processing Speed) an effect size (ES) of .30 is expected on the cognitive outcomes. Northey [48] conducted a meta-analysis on the effects of exercise interventions on cognitive function in adults older than 50. They found an overall ES of .29; when only participants are included without Mild Cognitive Impairment, the ES rose up to .36. Colcombe & Kramer [23] reported ES of almost .5 of fitness effects on cognitive functions in older adults. A meta-analysis of Chang [72] reported a lower ES = .10, though for all age groups, suggesting that the effect on cognitive performance in elderly is larger (ES = .18) than in young people. Therefore, we estimated an ES of 0.3 for our primary outcome measures of CF. An moderate ES (≥.30, Cohen [73]) is considered clinically relevant for practice.

The needed sample size has to be inflated to take account of the multilevel design. Therefore, an estimate of Intra Cluster Correlation (ICC) is used, based on the ICC of the previous Active Plus projects (ICC < .01). Statistical power analysis using G*Power [72] (ES = .30; power = .80; ICC = .01) showed that 190 participants per group are required. Based on our previous studies [45] we expect a 30% dropout rate at 12 months. We therefore will include 270 participants per group.

#### Statistical analyses

Independent t, Mann-Whitney U, and Chi-square tests are used to determine differences in baseline characteristics between the experimental group and the waiting list control group. To assess predictors of dropout, logistic regression with condition, baseline outcome measures, demographics, and degree of limitation regarding chronic conditions will be performed. Depending on the distribution of continuous, categorical, and interval outcomes, appropriate distribution and relevant statistical models will be used. These multilevel models will assess intervention effects on CF at end-of-intervention (6-months and 12-months) as well as the difference between 6- and 12-months measurements. To identify significant covariates, bivariate Pearson correlations are conducted between demographic variables and the independent and dependent variables of interest. Moderation analysis of type, duration, frequency and intensity of PA will be conducted. The most appropriate procedure for handling missing data will be selected after inspecting the amount and pattern of missing data.

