## Methods

### Study design

The study is a parallel, two-group cluster-RCT with a waiting list control group and assessments at baseline, six and 12 months. Due to the nature of the study, it is not possible to blind the researchers. Participants do not know there are two groups being examined. Ethical approval for the study was obtained from the Research Ethics Committee (cETO) of the Open University and the trial is registered with the Dutch Trial Register, protocol number NL6005. This protocol is reported in accordance with SPIRIT guidelines. The study is funded by a grant from the Brain Foundation Netherlands. All participants provide written informed consent prior to commencing the study. Participants may withdraw from participation at any time without giving an explanation, no data will be collected anymore. There are no interventions or care prohibited during the trial.

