### Participants

#### Recruitment

Five hundred and forty (540) participants are recruited over a period of 6 months through an invitation letter by one of the seven cooperating municipalities. Each municipality will select two groups for participation, who originate from one or more comparable residential areas or neighborhoods based on their socioeconomic status. Neighborhood selection is based on data of www.waarstaatjegemeente.nl, a website where municipalities can compare their own data with other municipalities on themes such as youth aid, finances and sustainability. These comparable neighborhoods are randomly assigned to either the experimental group or the waiting list control group [50]. Names and addresses of independently living men and women aged 65 years or older residing in these municipalities are drawn from the records of the residents’ registration office taking the General Data Protection Regulation of the European Union into account. The number of persons drawn from the records varied between 500 and 4000 per municipality.

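### Baseline arm comparisons use independent-sample tests although neighbourhoods are randomised, so their p-values, and the condition p-value in the dropout model if it has no cluster term, are too small when neighbourhoods differ within a municipality (minor)

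*Protocol article*

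**What the plan says.** The *Study design* section of the protocol article states: "The study is a parallel, two-group cluster-RCT with a waiting list control group". Under *Recruitment*, participants are approached "through an invitation letter by one of the seven cooperating municipalities", and "Each municipality will select two groups for participation, who originate from one or more comparable residential areas or neighborhoods". Allocation is then at area level: "These comparable neighborhoods are randomly assigned to either the experimental group or the waiting list control group".

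The *Sample size and statistical power* section accepts what follows from this: "The needed sample size has to be inflated to take account of the multilevel design". It uses an ICC of .01, reports that earlier projects with the programme had values below .01, and ends with "We therefore will include 270 participants per group".

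The *Statistical analyses* section opens with the arm comparison at baseline: "Independent t, Mann-Whitney U, and Chi-square tests are used to determine differences in baseline characteristics between the experimental group and the waiting list control group". It continues: "To assess predictors of dropout, logistic regression with condition, baseline outcome measures, demographics, and degree of limitation regarding chronic conditions will be performed". Multilevel models come afterwards and are tied to intervention effects on cognitive functioning (CF). No cluster term is named for the baseline comparison or the dropout regression.

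**The concern.** An independent t, Mann-Whitney U or chi-square test takes its reference distribution from about 540 independent people. In this trial whole neighbourhoods move between arms. Ordinary variation between neighbourhoods therefore enters the arm contrast, and the named tests have no term for it. The same holds for the condition coefficient in a logistic regression without a cluster term.

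The baseline comparison has a real job here. According to *Procedure*, residents are invited from neighbourhoods already designated experimental or control, so the comparison is the named check on whether recruitment produced comparable arms. The condition term in the dropout model is the named check on selective attrition, with 30% dropout expected. P-values that are too small would lead chance neighbourhood differences to be reported as recruitment imbalance or selective dropout more often than the nominal level implies.

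**Working it through.** **Inputs from the protocol article**
- Municipalities: 7, with two groups each, so 14 groups (*Recruitment*). This is a minimum, because a group may span several neighbourhoods.
- Participants: 270 per arm, 540 in total (*Sample size*).
- Planning ICC: .01, with values below .01 in earlier projects (*Sample size*). No ICC is given for baseline characteristics or dropout.
- Dropout: 30% at 12 months.
- Significance level and sidedness are not stated. Two-sided 5% is assumed for the baseline and dropout tests.

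**The plan's own sample size.** For effect size .30 and power .80, n per arm before inflation is 175 (two-sided 5%) or 138 (one-sided 5%).
- With m = 540/14 = 38.6, the design effect is 1 + 37.6 × .01 = 1.376. Then 138 × 1.376 = 189.8, which matches 190, whereas 175 × 1.376 = 241.
- Two-sided, 190 requires a design effect of 190/175 = 1.086, that is, clusters of about 9.6.
- For dropout, 190/0.7 = 272, close to the stated 270.

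The stated figure therefore does not settle which cluster size was meant, and the range below covers both.

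**Rejection rate of the unadjusted test.** Let ρN be the share of variance between neighbourhood groups within a municipality, ρM the share between municipalities, and m the cluster size. Municipalities are represented in both arms, so ρM cancels from the contrast. The true variance of the arm difference, relative to the variance the test assumes, is

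R = (1 − ρN − ρM) + m·ρN,

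which reduces to 1 + (m − 1)·ρN when ρM = 0. The rejection rate under no systematic arm difference is 2·[1 − Φ(1.96/√R)].

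| Setting | R | Formula | Simulated t-test |
|---|---|---|---|
| 14 groups, ρN = .01 | 1 + 37.6 × .01 = 1.376 | 9.5% | 9.45% |
| 14 groups, ρN = .005 | 1 + 37.6 × .005 = 1.188 | 7.2% | 7.0% |
| 14 groups, ρN = .001 | 1 + 37.6 × .001 = 1.038 | 5.4% | not run |
| 14 groups, ρN = ρM = .005 | .99 + 38.6 × .005 = 1.183 | 7.2% | 7.25% |
| 14 groups, ρN = 0, ρM = .01 | .99 | 4.9% | 4.5% |
| 28 clusters (m = 19.3), ρN = .01 | 1.183 | 7.2% | 7.4% |
| 56 clusters (m = 9.6), ρN = .01 | 1.086 | 6.0% | 5.9% |

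Each simulation used 10,000 trials, so its Monte Carlo standard error is about 0.2 to 0.3 percentage points. A control run with no clustering gave 5.1%.

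**Dropout.** For a 30% binary outcome with ICC .01 in 14 groups, a two-proportion (chi-square type) test rejected 9.4% of the time in 40,000 simulated trials. This bears on the condition term. Predictors that vary mainly between individuals are little affected.

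**Stronger clustering (assumed, not in the document).** With 14 equal groups, an ICC of .02 gives about 14% and .05 about 25%.

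**A test that respects the allocation.** A paired t-test on the seven within-municipality differences in group means rejected 4.2% to 5.3% of the time across the settings simulated (6,000 trials each).

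**The case against.** A reader might infer that these tests simply have twice their nominal error rate. The document does not support that as a fixed statement. The .01 is a planning value, earlier projects were below it, and it comes from the CF sample-size calculation. The number of clusters may exceed 14. Neighbourhoods are chosen to be comparable on socioeconomic status within a municipality, and variation shared within a municipality cancels between arms. All of this stands, and it is why the result has to be given as a range.

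A reader might also infer that the trial's main result is compromised. It is not. Effects on CF are to be estimated with multilevel models. The way missing data are handled is to be chosen after looking at their amount and pattern, and the text does not link that choice to the p-value for condition.

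On dropout, the article names a logistic regression and its predictors but does not exclude a cluster term, and an article may leave that detail to a fuller document. This also stands, so the dropout part is conditional and limited to the condition effect.

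The baseline sentence does not have that defence. It fixes specific independent-sample tests, and no fuller specification makes them account for clusters.

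**Conclusion.** The point holds, and it is minor. The named baseline tests do not match the allocation that the protocol itself describes and plans for. The direction of the error is clear: p-values are too small once neighbourhoods differ appreciably within a municipality (R exceeds 1 when ρN is more than ρM/37.6). The same applies to condition in the dropout model if it is fitted without a cluster term.

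The size is conditional. With two-sided 5% assumed and 14 equal groups, it is about 9.5% if the whole planning ICC of .01 lies between neighbourhoods within municipalities, and between about 5% and 9.5% for smaller ICCs or more clusters. There is no inflation if all the clustering lies between municipalities. It could be larger for characteristics that cluster more strongly, but the document gives no figure for these. The consequence is confined to how baseline balance and selective dropout are reported.

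**What to change.** In *Statistical analyses*, replace the independent-sample tests with a description of baseline characteristics by arm. Where a test is wanted, use one that respects the allocation, such as:
- a model with municipality and a neighbourhood-group random effect, with small-sample degrees of freedom; or
- a paired comparison of the seven municipality differences.

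Only the paired comparison was simulated here. The error rate of the model-based version was not checked and should be confirmed with so few groups.

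State that the dropout logistic regression includes the neighbourhood-group term, so that the condition effect has a cluster-valid standard error.

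The change needs no new data or participants, only wording and a little code. The real cost is precision. At the planning ICC with 14 groups, standard errors grow by √1.376 = 1.17, and the arm contrast has about 7 − 1 = 6 degrees of freedom. Intervals will be wider and the check less sensitive to true recruitment or dropout differences, so the descriptive differences should be read alongside any p-value.

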**Methods:**

A randomized controlled trial is performed, comparing the Active Plus intervention group to a waiting list control group. In total 540 older adults (≥65 years) with at least one chronic illness that limits mobility are recruited from 7 municipalities. Comparable neighborhoods within a municipality are randomly allocated to the intervention or control group. Baseline and follow-up measurements after 6 and 12 months assess cognitive functioning and physical activity behavior, measured both objectively with an accelerometer and subjectively with a self-report questionnaire. Multilevel analyses are conducted to assess effects on cognitive functioning, including analyses on moderation effects for physical activity type, frequency, duration and intensity.

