### Outcomes

As it is the main goal of the current project to test if the Active Plus program is able to increase CF or to slow down its decline by means of sufficient PA, the primary outcomes are CF and PA. Secondary outcome measures are self-reliance, health related quality of life, and loneliness. Outcomes are assessed at baseline, and after six and 12 months.

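### Covariates are picked by a significance screen on the trial's own data, from a pool of demographics that cannot yield the baseline test score; one fixed set should replace it

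*Protocol article*

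**What the plan says.** The Statistical analyses section states how covariates are found: "To identify significant covariates, bivariate Pearson correlations are conducted between demographic variables and the independent and dependent variables of interest". It gives no significance threshold. It does not say whether a variable must correlate with the independent variable, the dependent variable or both, nor which measurement occasion is used.

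The section Other relevant measures lists the candidate variables in these words: "Demographic and chronic disease related characteristics including age, gender, marital status, body mass index (BMI), educational level, income, degree of limitation regarding chronic illness(es) are" recorded.

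The effect models are described in one sentence: "These multilevel models will assess intervention effects on CF at end-of-intervention (6-months and 12-months) as well as the difference between 6- and 12-months measurements". Their levels, random effects and treatment of baseline are not given. Baseline outcome values are named as predictors only in the dropout analysis: "To assess predictors of dropout, logistic regression with condition, baseline outcome measures, demographics, and degree of limitation regarding chronic conditions will be performed". They are available for the effect models too, since "Outcomes are assessed at baseline, and after six and 12 months".

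On design, the abstract says: "Comparable neighborhoods within a municipality are randomly allocated to the intervention or control group". The Study design section says the researchers cannot be blinded. The Statistical analyses section also plans significance tests at baseline: "Independent t, Mann-Whitney U, and Chi-square tests are used to determine differences in baseline characteristics".

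**The concern.** This is a stated method, not a detail left for another document.

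- **The data choose the model.** Whether age or education enters depends on whether a correlation in this sample crosses a threshold. There are several cognitive outcomes (verbal learning, letter-digit substitution, trail making B-A, stop-signal reaction time) and two follow-up times, so the screen can return a different adjustment set for each. Estimates would then not be adjusted alike across outcomes.
- **The rule has several readings.** Correlated with the outcome, with the independent variable, with either, or with both are all consistent with the text. Unblinded analysts could settle on one after seeing results. Where the independent variable is allocation, the screen only detects chance imbalance, which does not identify prognostic variables.
- **The pool is too narrow.** The baseline score on the same test is not a demographic variable, and neither is the municipality within which neighbourhoods were allocated. The screen cannot pick either.

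A smaller point: Pearson correlation is acceptable for a binary variable such as gender but does not suit an unordered one such as marital status.

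At stake are a clear single analysis per outcome and, if baseline is not otherwise modelled, a good deal of precision.

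**Working it through.** **1. The plan's own figure.** Sample size and statistical power gives 190 per group for ES .30, power .80 and ICC .01. Alpha, sidedness and cluster size are not stated. At two-sided 0.05 without clustering:

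n = 2(1.960 + 0.842)² / 0.30² = 174.4, so 175 per group.

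190/174.4 = 1.089, a design effect that implies about 10 people per cluster. About 27 per cluster (380/14) would give 221. A one-sided 0.05 test with 540/14 = 38.6 per cluster also gives 190. The figure can thus be reached only with inputs the article does not state. It does not rest on covariate adjustment, so this point neither supports nor refutes it.

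**2. What the screen does to type I error.** Simulation with 4,000 runs per setting, 190 per arm, no clustering, six demographic variables explaining an assumed 15% of baseline-score variance, baseline-outcome correlation r of .5 or .7, and a screening threshold of 0.05:

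| Rule applied, no true effect | r = .5 | r = .7 |
|---|---|---|
| No adjustment | 0.050 | 0.053 |
| Correlated with outcome | 0.047 | 0.049 |
| With outcome or allocation | 0.046 | 0.048 |
| With outcome and allocation | 0.048 | 0.050 |
| Smallest p of these four | 0.060 | 0.064 |

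Across runs, the outcome-correlation reading chose 45 to 53 different covariate sets of the 2⁶ = 64 possible. With a true effect of .30, power was 0.84 with screened demographics, against 0.92 (r = .5) or 0.98 (r = .7) with a prespecified baseline score.

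**3. What baseline adjustment is worth if it would otherwise be absent.**

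- Completers per arm: 270 × 0.70 = 189 (270 per group and 30% dropout, both from the article).
- Cluster size, assumed: 7 municipalities × 2 groups = 14 clusters, so 378/14 = 27.
- Design effect: 1 + (27 − 1) × 0.01 = 1.26. Effective n per arm: 189/1.26 = 150.
- Baseline-outcome correlation r: not in the article, so a range is shown.
- Residual variance falls by r². Effective ES = .30/√(1 − r²). Noncentrality = effective ES × √(150/2). Two-sided 0.05.

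| r | Variance reduction | Effective ES | Power, 376 df | Power, 12 df |
|---|---|---|---|---|
| none | 0% | .300 | 0.736 | 0.665 |
| .3 | 9% | .314 | 0.775 | 0.706 |
| .5 | 25% | .346 | 0.849 | 0.786 |
| .6 | 36% | .375 | 0.900 | 0.846 |
| .7 | 49% | .420 | 0.952 | 0.915 |

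The 12 df column uses 14 clusters − 2 arms. Gains should be read within a column.

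**4. Municipality as a fixed effect.** With 14 clusters, 14 − 7 − 1 = 6 cluster-level df remain. With the design effect held at 1.26, power at 6 df is 0.707, 0.772 and 0.856 for r of .5, .6 and .7, lower than at 12 df. Between-municipality variance removed by the term would offset this, but the article gives no figure for it.

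**The case against.** The strongest reply is that the covariate sentence describes how extra demographic covariates are found and does not list every term in the model. The models are multilevel and outcomes are measured three times. Baseline may enter as a repeated measure or fixed adjuster, and municipality or neighbourhood as a level. A condensed article may leave that to the full plan. This stands. A reader might infer that the analysis omits baseline score and municipality; the article says neither that they are included nor that they are excluded.

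It can also be said that the screen does little harm to error rates. That stands too: one reading applied consistently was nominal in simulation, so a claim that the rule seriously distorts estimates or intervals is not supported. The power gains in step 3 measure the value of baseline adjustment, not damage done by the screen.

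Three further cautions hold. The independent variable need not be allocation alone, since the article also treats physical activity as a predictor of cognition. The article does not say that the baseline significance tests feed covariate choice. And because "Each municipality will select two groups for participation, who originate from one or more comparable residential areas or neighborhoods based on their socioeconomic status", the number of clusters may exceed 14, so 27 per cluster, the design effect and the 12 and 6 df are assumptions.

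None of this rescues the screen. It is written down, it is driven by the trial's data, and it is open to more than one reading.

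**Conclusion.** The stated covariate rule should be replaced. It lets the trial's data choose the adjusted model, allows a different model per outcome and time point, and leaves a choice of readings to unblinded analysts. The cost in type I error is small: nominal if one reading is fixed in advance, about 0.06 if the most favourable of four is taken, under a simulation without clustering. The rule also cannot select the baseline value of the outcome.

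The precision loss is conditional. If the multilevel model does not carry baseline in some other way, including it would raise power from 0.74 to 0.78–0.95, or from 0.67 to 0.71–0.92 with 12 df, for assumed r from .3 to .7, with residual variance falling by 9–49%. This rests on 189 per arm, ES .30 and an assumed design effect of 1.26. If baseline is already in the model, that gain is already secured and only the objection to the screen remains.

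**What to change.** Delete the sentence on bivariate correlations and put one fixed specification in its place, settled before follow-up outcomes are examined. Suggested content:

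> Every cognitive outcome is analysed with the same covariates: the baseline value of that outcome and a short named list (for example age, sex and educational level). Neighbourhood cluster is a level of the model, and repeated measurements are nested within participants. Baseline characteristics are reported descriptively by arm, without significance tests.

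If baseline is to enter as a repeated measure instead of a covariate, say so. If the moderation analyses need other covariates, name those separately.

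The model should also reflect allocation within municipality. The form is the trial statistician's choice: with about 14 clusters, municipality fixed effects would leave about 6 cluster-level df, a real trade-off against the variance they remove.

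The cost is wording only. The baseline scores and demographics are already collected, and municipality is known from recruitment. No change to sample size, visits or data collection follows.

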PA is complex behavior consisting of type of activity, duration, frequency, and intensity [47]. There are some indications that the beneficial effects of PA on CF are independent of these characteristics of PA [46]. However, another meta-analysis [48] showed that only a duration of > 45 min to ≤60 min per session at a moderate-to-vigorous intensity on as many days per week was beneficial for CF. Therefore, it is unclear what characteristics PA should have to be effective on CF in clinical practice. To provide more insight in this matter, we will study as another primary objective the relationship between the necessary type, frequency, duration and intensity of PA to increase CF or slow down its decline in the elderly with chronic illness(es) (ECI). To test PA behavior, we use both self-report questionnaires and accelerometers. Self-report questionnaires are known for overestimating PA, however they measure different constructs than accelerometers [49]. Therefore, both ways of measuring PA are administered in this project.

As mentioned before, elderly people with chronic illnesses have a lesser individual degree of independence and quality of life [12], and experience more feelings of loneliness [14]. Sufficient levels of PA and CF are important for self-reliance and a good health related quality of life (HRQoL) [3]. However, being sufficiently physically active is a great challenge for this target group [31]. Therefore, a secondary objective is to study the effects of the Active Plus intervention on self-reliance, HRQoL and loneliness.

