#### Experimental condition

The computer tailored Active Plus intervention stimulates PA among people aged 65 or over with a chronic illness and is proven to be effective in increasing PA behavior [37, 42–45]. The intervention is systematically developed using the Intervention Mapping Protocol, and based on various theoretical models such as the Theory of Planned Behavior [52], Precaution Adoption Process Model [53], the Integrated Model for Change (I-Change Model) [54], and a self-regulation model [55]. The intervention intents to take up and sustain PA behavior by influencing (pre−/post-) motivational constructs. The pre-motivational constructs addressed are awareness and knowledge among others. Constructs such as intention, social influence, intrinsic motivation, attitude and self-efficacy are addressed in the motivational stage. Post-motivational constructs include action planning, coping planning, strategic planning, commitment, and self-regulation skills. Especially for the targeted population of ECI tailored information is added on several chronic illnesses, the risks of sedentary behavior, and the benefits of PA for CF.

Participants in the experimental group receive advice on three occasions (see Fig. 1), tailored to the answers they give in questionnaires. The first personal advice is delivered right after the baseline assessment. Participants receive the second advice 2 months after the baseline questionnaire. And within 4 months after the baseline questionnaire feedback on progress in PA behavior is given, based on the second assessment (only used to generate a third advice). All participants in the experimental condition receive a copy of their personal advises by email (if they have registered an email address) and by mail as well. Participants receive an invitation for the follow-up assessment by mail, together with the follow-up questionnaire and a prepaid return envelope, and by email, including a link to the questionnaire.

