A great strength of this study is that the change in PA is measured both objectively with an accelerometer and with a self-report questionnaire. Questionnaires provide detailed insight regarding type of PA (e.g. household PA, leisure time PA), frequency and duration of specific PA behaviors. Such specific information is useful in targeting PA interventions and cannot be obtained from accelerometers. However, self-report PA questionnaires are known for their overestimation of PA which might occur due to misclassification of activities, double reporting, recall bias, and social desirability [74]. Accelerometers measure the quantity and intensity of movement. Although accelerometers result in objective PA measurements, they also have their limitations; they do not provide information on the type of activity and they are limited in the measurement of swimming/water-based activities, cycling, step/inclined activity, or strength exercises [74–77]. By using both methods we will gain optimal insight in type, frequency, duration and intensity of PA that is needed to increase CF or slow down decline of CF.

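### The only analysis named for the second primary objective, moderation by physical activity characteristics, cannot show which activity is needed to improve cognition

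*Protocol article*

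**What the plan says.** The Background sets the dose question beside the test of the programme itself: "we will study as another primary objective the relationship between the necessary type, frequency, duration and intensity of PA to increase CF" or to slow its decline. The Statistical analyses section gives this objective one sentence, "Moderation analysis of type, duration, frequency and intensity of PA will be conducted". The abstract's Methods paragraph describes the multilevel analyses of effects on CF in the same terms, "including analyses on moderation effects for physical activity type, frequency, duration and intensity". No other analysis of the PA–CF relation is named, and the time point of the PA moderator is not given.

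Elsewhere PA is described as what the programme changes. Under Experimental condition, Active Plus "stimulates PA among people aged 65 or over with a chronic illness and is proven to be effective in increasing PA behavior". Under Outcomes, CF is expected to change "by means of sufficient PA, the primary outcomes are CF and PA", and "Outcomes are assessed at baseline, and after six and 12 months". The Discussion stresses change over time: "A great strength of this study is that the change in PA is measured both objectively with an accelerometer and with a self-report questionnaire". It then says that using both instruments will show the PA needed to improve CF.

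**The concern.** A moderator of a treatment effect should not itself be changed by treatment. By the article's own account PA is a primary outcome and the route by which Active Plus should reach CF, so during follow-up it is an intermediate variable. Nobody is randomised to a type, duration, frequency or intensity of PA.

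A moderation term asks whether the programme's effect on CF differs across levels of PA. The objective asks how CF depends on PA. These are different questions. If the plan stands, one of two primary objectives has no analysis able to answer it. There is a further risk that PA coefficients from the moderation model are reported as dose findings of a randomised trial, although they compare people who chose their own activity level.

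**Working it through.** The article states no figure that decides this, so the check is first one of logic. A simulation then gives a sense of size.

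**Step 1: the two readings against the objective.**

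| PA used as moderator | What allocation × PA estimates | Answers which PA is needed? |
|---|---|---|
| Baseline | Whether the programme effect differs by starting activity; valid | No: it shows for whom the programme works |
| Follow-up, or change | Difference between arms in the PA–CF slope, given an outcome of allocation | No: a dose effect common to both arms gives an interaction of zero |

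The Outcomes and Discussion sections point to the second reading but do not fix it.

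**Step 2: inputs for the illustration.** From the article: 270 per group and 30% dropout, so 270 × 0.70 = 189 per arm. Assumed: the programme raises PA by 0.3 SD; an unmeasured health factor U loads 0.5 on PA and 0.4 on CF; PA (within arm) and the CF error-plus-health part have unit variance; two-sided 5% tests; clustering and baseline CF are left out. A is allocation (0 or 1) and b is the true PA effect:

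- PA = 0.3A + 0.5U + e
- CF = b·PA + 0.4U + e′
- Fitted model: CF on A, PA and A × PA

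**Step 3: does the moderation test see a dose effect?** With b = 0.3 the expected PA slope is 0.3 plus the confounding term (Step 4) in both arms, so the expected interaction is 0. Simulated rejection of the interaction is about 5% (5% to 7% over several runs, with and without confounding). That is the rate for a test with nothing to find.

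**Step 4: what happens to the PA slope if it is read as a dose effect?** With b = 0, the expected slope is (0.5 × 0.4) / 1 = 0.20 SD. Simulation gives 0.195 to 0.201, significant in about 77% to 80% of trials. The allocation coefficient given PA is biased by about −0.3 × 0.20 = −0.06 (simulated −0.03 to −0.07).

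If a measured proxy captures a share r of the variance of U, the slope becomes 0.20(1 − r) / (1 − 0.25r):

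- r = 0.5: 0.100 / 0.875 = 0.11, significant in about 35%
- r = 0.7: 0.060 / 0.825 = 0.07, significant in about 17%

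With other assumed loadings (0.3 to 0.5 on PA, 0.5 on CF) and no proxy, the null slope is 0.15 to 0.25, significant in 58% to 96%.

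**Step 5: false positives of the interaction itself, b = 0.** Rejection is 5% to 6% if uptake does not vary with health, and about 6% to 7% if the programme strengthens the health–PA link (an extra +0.3·A·U). If the programme weakens it (−0.3·A·U), rejection is about 15%. In that last case the intervention-arm slope is (0.2 × 0.4) / (0.04 + 0.75) = 0.10 against 0.20 in controls. The interaction is therefore about −0.10, and nearly all rejections are negative.

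**The case against.** The strongest reply is that the sentence is short, the article is condensed, and the moderator's time point and adjustment set may be settled in an analysis plan that is not shown. That stands as far as confounding is concerned: it arises only if follow-up PA is used and its slopes are read as dose effects. It does not rescue the method. The article itself names moderation as the analysis for a primary objective, and neither time point makes moderation answer it.

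A reader might infer that the planned test will tend to find beneficial doses even if PA does nothing. The calculation does not support that. The rejection rate near 79% belongs to the PA slope, not to the moderation test, which stays close to 5% except in one scenario where its errors run in the negative direction. The supported flaw is that the test is blind to dose.

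A reader might also infer that the programme's effect on CF is biased. The article does not name PA as a covariate in that comparison, so the first primary objective and the sample size basis are untouched.

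Two further points stand. Degree of impairment is measured, so a wholly unmeasured health factor is close to a worst case. And any adjusted PA–CF model, or mediation through PA, still assumes no unmeasured confounding.

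**Conclusion.** The point holds as a mismatch between a primary objective and its named analysis, whichever time point is meant. For follow-up PA or change in PA, the interaction test has about 5% rejection when PA truly has a 0.3 effect. PA slopes taken as dose effects could be about 0.20 SD under no effect, or 0.07 to 0.11 with a good measured proxy for health. The near-zero interaction follows from the model structure when the dose effect is the same in both arms. The slope sizes rest on assumed loadings and are illustrative. It should be fixed, but it does not threaten the randomised comparison of CF.

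**What to change.** In Statistical analyses, replace the moderation sentence with three statements.

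1. Moderation of the intervention effect on CF uses baseline PA characteristics only.
2. The dose question is addressed by a longitudinal model of CF at 6 and 12 months on PA characteristics. Within-person and between-person PA are separated, with adjustment for baseline CF, age, education and degree of impairment. SQUASH supplies type of PA, which the Discussion says accelerometers cannot give; SQUASH and the accelerometer both supply intensity and amount.
3. The dose results are observational, not randomised evidence, and residual confounding is possible, including from health that changes over time.

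Mediation of the allocation effect through PA may be added with the same caveat. The abstract wording should follow. The objective need not leave the primary set, provided its evidence is labelled this way.

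The cost is slightly more analysis and a weaker label for the dose conclusions. All the data are already planned.
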